## Abstract

**Background:**

To strengthen suicide prevention skills in mental health care in The Netherlands, multidisciplinary teams throughout the country are trained in the application of the new Dutch guideline on the assessment and treatment of suicidal behavior. Previous studies have shown beneficial effects of additional efforts for guideline implementation on professionals’ attitude, knowledge, and skills. However, the effects on patients are equally important, but are rarely measured. The main objective of this study is to examine whether patients of multidisciplinary teams who are trained in guideline application show greater recovery from suicide ideation than patients of untrained teams.

**Methods/Design:**

This is a multicentre cluster randomized controlled trial (RCT), in which multidisciplinary teams from mental health care institutions are matched in pairs, and randomly allocated to either the experimental or control condition. In the experimental condition, next to the usual dissemination of the guideline (internet, newsletter, books, publications, and congresses), teams will be trained in the application of the guideline via a 1-day small interactive group training program supported by e-learning modules. In the control condition, no additional actions next to usual dissemination of the guideline will be undertaken.

Assessments at patient level will start when the experimental teams are trained. Assessments will take place upon admission and after 3 months, or earlier if the patient is discharged. The primary outcome is suicide ideation. Secondary outcomes are non-fatal suicide attempts, level of treatment satisfaction, and societal costs. Both a cost-effectiveness and cost-utility analysis will be performed. The effects of the intervention will be examined in multilevel models.

**Discussion:**

The strengths of this study are the size of the study, RCT design, training of complete multidisciplinary teams, and the willingness of both management and staff to participate.

**Trial registration:**

Netherlands trial register: NTR3092

## Background

To strengthen suicide prevention in mental health care in The Netherlands, the Dutch multidisciplinary practice guideline on the assessment and treatment of suicidal behavior (PGSB) has been developed by representatives from the Dutch Association of Psychiatrists (NVvP), the Dutch Association of Psychologists (NIP), the Dutch Nurses’ Association (V&VN), and supported by the Dutch Knowledge Centre on Mental Health and Addiction (Trimbos Institute)
[1]. The PGSB combines the stress-diathesis model
[2] and the entrapment model
[3] to explain the onset of suicidal behavior. It consists of chapters on the theoretical concept of suicidal behavior, basic assumptions of professional practice (fostering a therapeutic alliance with the suicidal patient, providing continuity of care and safety, and a systematic assessment of suicidal behavior), treatment of suicidal behavior, and professional practice following a suicide. Importantly, suicidal behavior is considered the focus of treatment. The guideline was issued in May 2012
[1].

One consistent finding in the literature is the gap between guideline development and the application of guidelines in daily health care practice
[4-6]. As a consequence, patients do not always receive appropriate care
[6,7]. Grol and Grimshaw (2003) suggested that structured implementation can improve adherence to guidelines
[6]. Despite its importance, implementation science is still just emerging
[8]. Theory-based and tailored implementation approaches are widely developed and studied
[9] but no ‘magic bullet’
[10] to improve health care has been found to date. Knowledge of effective strategies is limited, whether from highly controlled studies with limited external validity, or from field studies with no significant effect or small effect sizes. Moreover, patient outcomes are rarely assessed in implementation studies. Regarding implementation in psychiatry, two systematic reviews
[11,12] showed a modest effect of implementation of psychiatric guidelines on care and patient outcome, and concluded that there is a need for more studies on the effects of guideline implementation at both a patient and professional level. Overall, there is limited empirical evidence on the most effective strategy to implement guidelines in general
[6,8,9], in particular in mental health care
[11,12].

Considering the importance of the PGSB, the evidence on non-adherence to guidelines, and the lack of evidence-based implementation strategies, the Dutch government commissioned a study on the effectiveness of the implementation of the PGSB. In 2011, the PITSTOP suicide (professionals in training to stop suicide) study started to examine the effect of a multifaceted, e-learning supported train-the-trainer implementation (TtT-e) program delivered to multidisciplinary teams of mental health care departments in a randomized cluster trial.

The content of the TtT-e program is based on the PGSB. In the TtT-e, senior staff members are trained by suicide experts. Subsequently, trained staff members train their multidisciplinary teams, using role play and personalized feedback.

The effectiveness of the TtT-e program on guideline implementation is expected since research has shown that small group training on suicidal behavior assessment with role play and personalized feedback leads to improved professional confidence and effective professional behavior
[13]. Also, since suicide prevention in mental health care is essentially multidisciplinary, professionals are trained in multidisciplinary groups
[4]. The training is supported by an e-learning module as e-learning is considered to complement face-to-face training in medical settings; Ruiz *et al*. reported that e-learning helped medical students become more actively involved in the study material, and thereby helped to internalize the material
[14].

The PITSTOP suicide study aims to evaluate the effect of the TtT-e program at both a patient and professional level. The design of the study at the professional level has already been published
[15] and the outcomes will be presented in a separate article. This article describes the protocol for the patient-level study.

The TtT-e program aims to strengthen the competences of health care professionals. The primary outcome of the present study is suicide ideation of patients due to improvement of professional skills. Professional and gatekeeper training in diagnosis and treatment of depressive disorders, which are associated with suicidal behavior
[16], have been shown to result in a reduction of suicide rates when delivered to general practitioners
[17-19]. A reduction of self-destructive acts in adolescents of an American Indian Tribal Nation was found after a suicidal behavior program
[20], and a suicide prevention program in the US Air Force personnel resulted in a decline of the suicide rate
[21]. However, the effects of professional or gatekeeper training programs on suicide rate and suicidal behavior are investigated in non-randomized controlled study designs. As a result, the research conducted to date does not clearly demonstrate whether professional or gatekeeper training has unique and independent effects on actually reducing suicidal behavior.

Due to increasing budget constraints and rising costs of mental health care, evidence on effectiveness alone is not sufficient for policy making. Policy makers aim to maximize health benefits from the budget available and, therefore, need information on both the costs and effects of the interventions. Thus, an economic evaluation to provide this information will also be performed. Most economic evaluations of guideline implementation strategies have methodological deficits and do not consider all relevant costs and benefits
[22]. In the current study, we will estimate both the treatment and policy cost-effectiveness of the TtT-e program in comparison with usual care, as described by Mason *et al*.
[23]. We will report the outcomes of the economic evaluation in a separate article.

In sum, the primary outcome of the current study is recovery from suicidal ideation. We hypothesize that patients treated by multidisciplinary teams who are trained by the TtT-e program will recover more quickly from suicidal ideation as compared with patients treated by multidisciplinary teams who were not trained.

Secondary outcomes are non-fatal suicide attempts and satisfaction with treatment. We hypothesize that patients in the intervention condition will report fewer non-fatal suicide attempts and more satisfaction with treatment than patients in the control condition.

A further aim of this study is to evaluate the cost-effectiveness and cost-utility of the intervention. We hypothesize that the intervention will be more cost-effective compared with implementation as usual (IAU).

## Method

### Design

This is a multicentre cluster randomized controlled trial (RCT) in which multidisciplinary teams from mental health institutions (MHIs) are matched in pairs with respect to patient diagnoses and average treatment duration. Subsequently, pair members are randomly allocated to treatment conditions.

A MHI is a regional organization with a specific catchment area of patients
[24]. For example, in 2011, MHI Rivierduinen had a catchment area of 1.1 million people within an area of approximately 1,500 km^2^ in the region of South Holland. MHI Rivierduinen has 44 psychiatric departments and treats an overall number of 24,753 patients annually with 2,726 employees
[25]. Most of the psychiatric departments are specialized in the treatment of patients of specific diagnostic categories, such as depression or personality disorder.

### Recruitment

Recruitment of MHIs took place during meetings and conferences on suicide prevention in The Netherlands between 2008 and 2010. MHIs were invited to participate in the study. When MHIs expressed willingness to participate, they were requested to indicate at least two multidisciplinary departments for adult care to be included in the study. To prevent exchange of training materials between the experimental and control condition, MHIs were explicitly asked to provide departments that were based in separate buildings and/or on separate locations, and to be sure that staff members were not exchanged or shared between departments. This resulted in 43 participating departments distributed over 10 MHIs (Figure 
1). Various types of mental health care departments are represented in the study (inpatient and outpatient care, crisis departments, and long-stay departments) treating patients of various diagnostic categories (personality disorder, depressive disorder, anxiety disorder, and psychotic disorder) and of various ages.

**Figure 1 F1:**
[figure not shown]
**Overview of the ten MHIs.** The number of departments and the primary patient group per department are indicated. MHI, mental health institution.

### Measurement procedure

At patient level, the preferred mode of data collection is by routine outcome monitoring (ROM), an online system by which data on the effectiveness of treatment in everyday clinical practice are systematically collected
[26]. In MHIs not using ROM, graduate students and/or research assistants will use paper and pencil questionnaires to collect data. The results from the graduate students/research assistants are expected to be comparable to the data collected via ROM. ROM also works with assistants to collect data and help participants to understand items/instructions
[26]. Using differential item functioning (DIF)
[27], we will investigate if the findings are indeed comparable, and control for any bias due to difference in data collection in the final analysis. By collecting data either via the ROM or graduate students/research assistants, we aim to reach all newly admitted patients in the participating departments. As the intervention focuses on fostering a working relationship with suicidal patients, the intervention is expected to be most effective during the first month of treatment. Therefore, patients will be assessed directly at admission (T0) and at 3 months after admission (T1) (Figure 
2). If a patient is discharged within 3 months, T1 will be arranged just before discharge. Measurements in the experimental departments will start immediately after all staff are trained. In the control departments, T0 will start when the department is informed of the allocation outcome. All eligible patients will be informed about the study and will be asked to provide written informed consent.

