### Intervention

In the experimental condition, the complete multidisciplinary teams (all registered nurses, psychologists, physicians, and psychiatrists) will be trained in the application of the guideline via the TtT-e program. By training complete multidisciplinary teams, including all team members, irrespective of full- or part-time staff, we aim for 100% coverage. In the TtT-e program, three types of actors are involved: masters, trainers, and trainees. The training is applied on two levels: first, trainers are trained by masters. Subsequently trainees are trained by trainers. The training program is supported by two e-learning modules. The first module is developed for trainees. It consists of video vignettes in which experienced nurses, psychologists, and psychiatrists interact with suicidal patients (played by actors). The total running time of this module for trainees is 60 minutes. In addition to the e-learning module for trainees, a second e-learning module was developed specifically for trainers. It provides a video of the first training session provided by masters to trainers, which was processed into an e-learning format allowing trainers to review the training session.

The TtT-e is a 1-day small interactive group program supported by e-learning modules, which reflects the PGSB recommendations
[1]. The PGSB recommendations served as the starting point to set the content of the TtT-e program within the PITSTOP suicide study. First, all guideline recommendations were listed and clustered into six themes: 1) basic clinical skills when discussing suicidality; 2) systematic assessment of suicidal behavior; 3) diagnosis of the current suicidal condition; 4) safety and continuity of care, including participation of the patient’s relatives; 5) treatment of suicidal behavior; and 6) chronic suicidal conditions. Second, clusters were transformed into six modules and scheduled according to the sequence of action in common clinical practice. For each module, goals and competences were set in terms of professional behavior. Furthermore, the PGSB recommends systematic investigation of the suicidal condition of patients by using the Chronological Assessment of Suicidal Events (CASE) interview

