#### Statistical analyses

As the study is a design with different levels, all outcomes will be analyzed using multilevel models. Patients are nested within departments (level 1), and departments are nested within MHI centers (level 2). Multilevel models are hierarchal systems that estimate random coefficients and variance components for each level
[33]. Random intercepts will be included in the multilevel models. Data will be analyzed on an intention-to-treat basis.

To examine the hypothesis that suicide ideation in patients of professionals who received the TtT-e program is more likely to be reduced than patients of professionals who did not receive TtT-e, we will compare changes in BSS scores between patients of teams allocated to the intervention with patients of teams in the control group. To examine differences in the number and intensity of suicide attempts, scores on items 20 and 21 of the BSS will be dichotomized (YES/NO, LOW/HIGH) and compared between treatment groups using logistic regression. To examine the effect of the intervention on treatment satisfaction, mean scores of the four satisfaction items between groups will be compared. For the economic evaluation, missing cost and effect data will be imputed using multiple imputation according to the MICE algorithm
[34]. The results of the imputed datasets will be pooled using Rubin’s rules
[35]. Bias-corrected and accelerated bootstrapping with 5,000 replications will be used to estimate 95% confidence intervals around the mean difference in total costs between the treatment groups. Incremental cost-effectiveness ratios (ICERs) will be calculated by dividing the difference in mean total costs between the treatment groups by the difference in mean effects between the treatment groups. Bootstrapping will also be used to estimate the uncertainty surrounding the ICERs, which will be graphically presented on cost-effectiveness planes. Cost-effectiveness acceptability curves will also be estimated. Cost-effectiveness acceptability curves will show the probability that the intervention is cost-effective in comparison with usual care for a range of different ceiling ratios (that is, the willingness to pay for one extra unit of effect)
[36].

Approval was obtained from the Medical Ethics Committee of the VU University Medical Centre, Amsterdam, The Netherlands (registration number: 2011/151). All local medical ethics committees agreed with this approval.

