1 demonstrates that the included departments are located in urban and rural regions of The Netherlands. We conclude that the included departments provide a representative sample of all departments in mental health care institutions in The Netherlands. We will compare the patient characteristics of the sample with the national patient population available via the Dutch Association of Mental Health and Addiction Care (GGZ Nederland, Amersfoort, The Netherlands), and will describe the results to check external validity.

A possible limitation of the study is that budget cuts, reorganizations, and layoffs, commonplace in Dutch mental health care, may interfere with the study aims. Attrition of patients to the study is a further challenge, since not all patients will complete the ROM at all intervals due to the lack of time of professionals or inexperience with the ROM
[37]. Using a strict protocol and local research assistants/nurses, we aim for limited drop-out. To prevent drop-out, research assistants will help patients to complete the questionnaires and will make appointments for follow-up assessment.

Commitment of both management and employees of the participating MHIs is crucial. To date, willingness of both management and employees to apply the TtT-e program is excellent. The findings from the current study may be generalized to implementation of other (mental) health care guidelines.

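### Patient assessment opens on a different trigger in each arm, so control patients will tend to be recruited earlier and arm is partly confounded with calendar time

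*Protocol article*

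**What the plan says.** All of this is in the Protocol article.

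- **Measurement procedure, experimental arm:** "Measurements in the experimental departments will start immediately after all staff are trained".
- **Measurement procedure, control arm:** "In the control departments, T0 will start when the department is informed of the allocation outcome".
- **Who enters:** "we aim to reach all newly admitted patients in the participating departments". The opening date therefore decides which patients represent each arm.
- **Intervention:** training is sequential, "first, trainers are trained by masters. Subsequently trainees are trained by trainers". Coverage is a target: "irrespective of full- or part-time staff, we aim for 100% coverage".
- **Abstract, Methods/Design:** "Assessments at patient level will start when the experimental teams are trained". Control departments are not mentioned separately.
- **Statistical analyses:** "Data will be analyzed on an intention-to-treat basis".
- **Discussion:** "budget cuts, reorganizations, and layoffs, commonplace in Dutch mental health care, may interfere with the study aims".

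The text shown gives no date for the notice to control departments, no duration for the training roll-out, no closing date for recruitment, and no rule for a department whose training is delayed or incomplete.

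**The concern.** In a parallel cluster trial, both arms should be observed over the same period, so that changes in usual care, season and case mix fall on both alike. Here the control clock starts at an administrative notice and the experimental clock starts at the end of a training programme. The experimental arm would then be observed later on average. The article itself gives reasons to expect change over that time. The guideline was published in May 2012 and is being disseminated to both arms, and mental health services are under financial and organisational pressure.

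A second consequence follows from a literal reading. An experimental department can supply patients only once its whole team has been trained, and a control department faces no such condition. If some department never reached that point, it would yield no data while its matched partner did. That would sit badly with the stated intention-to-treat analysis.

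**Working it through.** **1. The start rules side by side.**

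| | Control | Experimental |
|---|---|---|
| Trigger | Notice of allocation | Whole team trained |
| Steps between allocation and opening | Notice only | Masters train trainers, trainers train the team, every member finishes |
| Depends on completed training | No | Yes, read literally |

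Controls open first unless their notice is delayed until about the time the partner finishes training. The text neither provides for that delay nor rules it out.

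**2. The plan's own figure.** Inputs from Sample size: d = 0.3, alpha 0.05 (taken as two-sided), power 0.80, 20% correction for clustering. The t-based calculation gives 176 per arm, and 2 × 176 × 1.2 = 422.4, rounded up to the stated 423. The point does not change this number. It supplies the precision used below: effective size 423/1.2 = 352.5, or 176.25 per arm, and SE = √(2/176.25) = 0.107 SD.

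**3. Illustrative shift from drift.** Shift = lag × drift. Two-sided type I error = 1 − Φ(1.96 − shift/SE) + Φ(−1.96 − shift/SE). Lag and drift are both assumptions. Drift means drift in the analysed outcome, the change in BSS.

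| Assumed lag | Assumed drift per month | Shift (SD) | Share of d = 0.3 | Type I error |
|---|---|---|---|---|
| 1 month | 0.01 | 0.01 | 3% | 0.051 |
| 3 months | 0.01 | 0.03 | 10% | 0.059 |
| 3 months | 0.02 | 0.06 | 20% | 0.087 |
| 6 months | 0.02 | 0.12 | 40% | 0.203 |
| 6 months | 0.05 | 0.30 | 100% | 0.804 |

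The sign is open. A shift of 0.06 SD could add to a true 0.30 (giving 0.36) or take from it (giving 0.24).

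**4. Illustrative overlap within a pair.** Assume each department closes at the planned average of 20 patients and admits r patients per month. Its window is 20/r months, and overlap = max(0, 1 − lag × r/20). At a 3-month lag:

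- r = 2: 1 − 6/20 = 70%
- r = 5: 1 − 15/20 = 25%
- r = 10: 1 − 30/20 is negative, so 0%

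Admission rates are not in the article. At high rates, adjustment for admission date would have to borrow from other pairs or extrapolate.

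**5. If an experimental department never opened.** Table 1 lists 21 experimental and 22 control departments. Take 423 split equally, remove 20 patients per lost experimental department, and keep the 20% correction. Power = Φ(0.3/√(1/n_c + 1/n_e) − 1.96), with n_c = 176.25 and n_e = (211.5 − 20k)/1.2:

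- k = 0: 0.80
- k = 1: n_e = 159.6, power 0.78
- k = 3: n_e = 126.3, power 0.73
- k = 5: n_e = 92.9, power 0.65

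The power loss is modest for one or two departments. Loss of randomised comparability would matter more, since departments able to train everyone may differ from those that are not. The article does not report that any department was lost.

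**The case against.** **The lag may be small.** Training is a one-day programme with a 60-minute e-learning module for trainees, and control departments may have been told their allocation at about the time their partners finished. The study-design figure is not available here and may carry a timeline. This stands as to size: the lag is unknown. It does not remove the point, because the written rule neither bounds the lag nor secures overlap.

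**Change scores remove some drift.** The primary analysis compares changes in BSS, so differences over time in average severity at admission are partly removed. This stands. Only drift in the amount of change over the follow-up of up to 3 months biases the contrast.

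**The bias might be taken to favour the intervention.** The document does not support that. Guideline spread would help the later arm, whereas cuts and layoffs would plausibly harm it, so the direction is not established.

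**A reader might infer that untrained departments are dropped from the intention-to-treat analysis.** No section says so. It is only a consequence of the start rule read literally, and handling of delayed training may be set out in the full protocol or analysis plan. The absence of a calendar-time term from the article's model description is no fault either, for the same reason.

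**A reader might infer that the Abstract contradicts the Measurement procedure.** The Abstract's sentence is condensed. It can be read as one common start, which would not agree with the control rule, but it is not an explicit second rule. The two should be worded alike.

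**Aligned starts have a price.** A start date that does not wait for the last trainee may dilute exposure. That is fair and is counted under the fix.

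**Conclusion.** The point holds as a weakness in the recruitment rule. Different triggers by arm, sequential training after allocation and entry by new admission together mean that control patients will tend to come earlier unless control notice is delayed, and the text provides for no such delay. Arm and calendar time are then partly confounded. An analysis plan can adjust for this where the windows overlap, but it cannot create concurrent controls where they do not.

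No bias has been demonstrated. Under assumed lags of 1 to 6 months and drifts of 0.01 to 0.05 SD per month, the shift runs from 0.01 to 0.30 SD, or 3% to 100% of the target effect. That range shows how little the document fixes, and it is not an estimate. The intention-to-treat part is conditional: it matters only if some experimental department failed to complete training. The change is worth making because it is specific and costs little.

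**What to change.** 1. **Departments not yet open** (Trial status says recruitment is ongoing): start T0 in both members of a matched pair on the same calendar date, the scheduled end of training of the experimental member, and keep that date if training slips. With 21 experimental and 22 control departments, at least one control has no experimental partner, so state its start date separately.
2. **All departments:** follow every randomised department and analyse it as allocated, whether or not training was completed.
3. **Wording:** bring the Abstract and the Measurement procedure to this one rule.
4. **Data already collected:** adjust the primary multilevel model for admission date, add an analysis restricted to each pair's common recruitment window, and report start dates by arm.

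The cost is a protocol clarification, one covariate and one date-restricted analysis; the planned 423 need not change. The downsides are real. The restricted analysis loses some early control patients, a fixed start may include patients treated before all staff are trained, and experimental patients who were never assessed cannot be recovered.
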